Breast cancer is strongly influenced by female sex hormones such as oestrogen and progesterone; both by those produced naturally in a woman's body (endogenous hormones), and by hormones taken for contraception or as hormone therapy for the menopause (HT) (exogenous hormones). Current users of both hormonal contraceptives and HT have an increased risk of breast cancer, up to 2-fold in the case of HT preparations containing both oestrogen and a progestagen (synthetic progesterone). Understanding these risks has direct implications for public health: for example, rates of breast cancer have fallen in response to falls in prescribing of HT, following publication of reliable evidence on breast cancer risk in recent years. There are however some gaps in our knowledge. It has been suggested that the effect of HT on breast cancer risk may depend on the timing of use (in relation to age or menopausal status); and there is limited information on the risks associated with progestagen-only contraceptives, or with specific contraceptive formulations. The GPRD's large size and the availability of detailed prescription data by type will allow us to examine these questions; our analyses would extend and supplement previous GPRD studies of hormone use and breast cancer.

Objectives, specific aims and rationale

*Research objective:* to obtain relative risks for incident breast cancer in relation to prior prescribing of contraceptive hormones and of hormone replacement therapy for the menopause (HT), by type and timing of use.

*Specific aims:* to add to existing knowledge about the effect of use of exogenous female sex hormones on risk of breast cancer, examining unanswered questions including the influence on risk of the timing of HT use, and suggested differences in risk associated with specific contraceptive preparations.

*Rationale:* current use of both HT and contraceptive hormones has been shown to increase risk of breast cancer, and this knowledge has direct public health implications. The large size and reliable prescribing information in the GPRD will allow us to add to existing knowledge by examining breast cancer risk in relation to specific hormone preparations and to timing of HT use, where there is at present suggestive but unconfirmed evidence for differences in risk.

Background

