Exposure: patients will be considered exposed to exogenous hormones if they have at least one prescription for a hormonal contraceptive or hormone replacement therapy preparation (as defined in the British National Formulary (BNF)) within the observation period (start of follow-up to index date). Sensitivity analyses will be performed restricting the definition of exposure to those with 2 or more prescriptions. OC/HT type will be assigned based on BNF classification, classing women with separate prescriptions on the same day for oestrogen and progestagen as being prescribed combined oestrogen-progestagen therapy.

Outcomes: incident invasive and *in situ* cancers of the breast (ICD-10 C50 and D05)

Covariates: smoking status, alcohol drinking [most recent record before index date], body mass index [most recent record at least 2 years before index date, to account for reverse causality] and parity will be taken into account where possible in adjusted and/or stratified analyses. Availability of prescription data will allow medications such as aspirin and bisphosphonates, which may be related to breast cancer risk and to hormone use, to be considered in supplementary analyses.

Data/statistical analysis outline methodology

Conditional logistic regression will be used to estimate crude and adjusted odds ratios (relative risks) with 95% confidence intervals for cancer risk in relation to hormone prescription vs no prescription within the observation period. Analyses for hormonal contraceptives will include hormone type and mode of delivery, including progestagen-only contraception; for HT, hormone type, mode of delivery and timing of use; for both, the risks associated with use of Mirena will be examined. Adjustment variables will include smoking status (never, current, past, unknown), alcohol drinking (none, some, unknown) and body mass index (<25, 25-30, 30+ kg/m sq, unknown) and where possible, parity (at least nulliparous, parous, unknown). Data analysis will be carried out using STATA software v10. Analyses for HT will generally be restricted to women aged over 40, and for OC use to women aged 20-50 years.

Patient/user group involvement

None

Limitations of study design, data sources, analytic methods

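### The OC analysis shares ages 41-50 with the HT analysis, but the adjustment set omits the other hormone class and the unexposed group is not clearly defined, so HT use can distort the OC odds ratio

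*Protocol*

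**What the plan says.** Four statements in the protocol bear on this point.

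- **Age ranges** (Data/statistical analysis outline methodology): "Analyses for HT will generally be restricted to women aged over 40, and for OC use to women aged 20-50 years". Ages 41-50 belong to both.
- **Adjusters** (same section): "Adjustment variables will include smoking status (never, current, past, unknown), alcohol drinking (none, some, unknown) and body mass index", and "where possible, parity (at least nulliparous, parous, unknown". Each is given with its categories. No hormone term is listed.
- **Exposure** (Exposures, outcomes, covariates): a woman is exposed if she has "at least one prescription for a hormonal contraceptive or hormone replacement therapy preparation" between the start of follow-up and the index date. The definition pools the two classes.
- **Contrast** (outline methodology): "cancer risk in relation to hormone prescription vs no prescription within the observation period". It does not say whether the unexposed are free of both classes or only of the class under study.

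Other drugs are mentioned: "Availability of prescription data will allow medications such as aspirin and bisphosphonates, which may be related to breast cancer risk and to hormone use" are to be considered in supplementary analyses, and the limitations section says that bisphosphonates and NSAIDs can be handled to some extent by stratification. Neither place mentions the other hormone class. The 2017 amendment updates the data and the case and control definitions and leaves this unchanged.

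The protocol regards both classes as risk factors. Its summary states: "Current users of both hormonal contraceptives and HT have an increased risk of breast cancer". The Background gives about 1.3 for current combined OC use and about 2 for current combined HT.

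**The concern.** In the OC analysis, HT is a measured exposure for which the protocol itself quotes a larger relative risk than for OC, and the listed model leaves it out. Exposure is any prescription during observation, so a woman who moves from a contraceptive to HT counts under both classes.

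The consequence depends on the unexposed group:

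- **Neither class.** The reference is clean, but OC users who also had HT remain in the exposed group, and their HT effect is credited to OC. The odds ratio rises whenever there are dual users and HT raises risk. No association between the two uses is needed.
- **No OC only.** HT users sit on both sides of the comparison. The OC odds ratio is confounded unless HT and OC use are independent within matched sets, and the direction follows the sign of the association.

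The expected OC effect is modest, so even a moderate proportional shift matters for its interpretation.

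**Working it through.** The protocol has no figure for this bias. Its power statement (detectable relative risk below 1.1 overall, at most 1.5 at 1% exposure) reproduces and is not in dispute. With 10,000 cases, an unmatched approximation gives 1.068, 1.080 and 1.335 at exposures of 33%, 20% and 1% with four controls per case, and 1.075, 1.088 and 1.372 with two.

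**Simple calculation for the OC odds ratio**

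From the Background: OC odds ratio 1.3, and an HT relative risk of 2.0 as the upper value. Assumed, because the protocol gives no figure:

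- HT relative risk of 1.5 as the lower value, since any prescription may carry less risk than current use.
- Weight w = 0.8 for ages 41-50, taken as the share of 20-50 cases in that band.
- In women aged 41-50, a share p = 10-20% of OC users also prescribed HT (reference = neither), or HT prevalence of 20% in OC non-users and r times that in OC users (reference = no OC).

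Reference = neither class: observed OR = 1.3 × [1 + w·p·(RR − 1)]

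Reference = no OC: observed OR = 1.3 × [1 + w·r·0.2·(RR − 1)] / [1 + w·0.2·(RR − 1)]

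| Reference | Inputs | Calculation | Observed OC OR |
|---|---|---|---|
| Neither | p = 0.1, RR = 1.5 | 1.3 × 1.04 | 1.35 |
| Neither | p = 0.2, RR = 2 | 1.3 × 1.16 | 1.51 |
| No OC | r = 0.5, RR = 1.5 | 1.3 × 1.04/1.08 | 1.25 |
| No OC | r = 0.5, RR = 2 | 1.3 × 1.08/1.16 | 1.21 |
| No OC | r = 0, RR = 1.5 | 1.3 × 1/1.08 | 1.20 |
| No OC | r = 0, RR = 2 | 1.3 × 1/1.16 | 1.12 |
| No OC | r = 1, any RR | 1.3 × 1 | 1.30 |

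Strictly, w should be the share of OC-informative matched sets aged 41-50. If OC use is commoner in younger women, that share is below the share of cases. Halving w to 0.4 gives 1.3 × 1.02 = 1.33 to 1.3 × 1.08 = 1.40 for the neither reference.

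**Cross-check with a joint 2×2 model**

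This model takes multiplicative odds ratios of 2.0 (HT) and 1.3 (OC), 20% OC prevalence, and an assumed HT-OC odds ratio among controls of 0.25 to 4. Each class is analysed without the other.

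- OC, HT prevalence assumed 10%: 1.20-1.49 (reference no OC), 1.34-1.60 (reference neither).
- OC, HT prevalence 33%: 1.07-1.64 and 1.47-2.07. The protocol's 33% is for women over 40, so these ranges cannot be carried over to ages 20-50 and only show an extreme.
- HT, at 33% HT and 20% OC: 2.00 becomes 1.90-2.14 (reference no HT) or 2.05-2.22 (reference neither). The 20% is the protocol's figure for ages 20-50. At an assumed 5% OC prevalence the two ranges together are 1.97-2.06.
- With independent use and a class-only reference, both return unbiased: 1.30 and 2.00.

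**The case against.** **It can be left to the analysis plan.** The section is an outline, the list opens with a phrase that does not make it exhaustive, the age limits apply only generally, and covariates may be handled by stratification. A later plan could add the term. That stands in part. But the protocol fixes its adjusters down to their categories and names secondary drugs such as aspirin, so leaving out the other study exposure is a feature of the stated model. A plan that followed the list as written would carry the problem forward.

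**The inputs are assumed.** This stands. The 80%, the 10-20% dual use, and the 20% HT prevalence with its halving in OC users are not in the protocol. The Background's relative risks are for current use, while exposure here is any prescription. The figures show plausible size; they do not estimate the bias.

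**The literal reading of unexposed is neither class.** It is the more natural reading, since the exposure definition pools the classes. It removes HT users from the reference group but does not remove dual users from the exposed group.

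A reader might infer three stronger things that the documents do not support:

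- *Both odds ratios are certainly biased.* Bias needs dual users kept as exposed against a hormone-free reference, or an HT-OC association within matched sets. The protocol gives no dual-use frequency and no such association, and the HT odds ratio moves little.
- *The problem lies only at ages 41-50.* For HT it does not: women over 50 with long records can have earlier OC prescriptions.
- *The bias is as large as the differences between contraceptive preparations.* The protocol gives no expected size for those differences. If HT co-use is similar across preparations, much of a shared bias cancels between them.

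**Conclusion.** The point holds for the OC analysis and should be corrected before analysis. If the stated model is followed, a true OC odds ratio of 1.30 would be reported as about 1.35-1.51 with a neither-class reference, 4% to 16% too high. With a no-OC reference it would be about 1.12-1.25 if HT is less common in OC users, 4% to 14% too low; it would be too high if HT is more common in them, and unbiased if the two uses are independent within matched sets. The direction therefore depends on a definition that the protocol leaves open. The sizes rest on the assumptions listed and shrink if fewer of the OC-informative sets are aged 41-50.

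For HT, the same omission probably has a small effect, from 2.00 to 1.90-2.22 even with a generous OC prevalence and a wide range of association.

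**What to change.** In the analysis section, state whether unexposed means no prescription of either class or none of the class under study. Then do one of the following:

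1. Add prescription of the other class in the observation period (HT by type in the OC models) as an adjustment variable in both the OC and the HT models. The reference must then be the class-specific one, because a reference free of both classes leaves no unexposed women with the other class.
2. Fit one exposure variable with levels OC only, HT only, both and neither, with neither as the reference. This needs a stated rule for classifying Mirena, which the protocol examines under both headings.

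Add a sensitivity analysis that drops women prescribed both classes.

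Both exposures already come from the same prescription records, so no new data are needed. The cost is one extra model term, one classification rule and a very small loss of precision.

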Reliable analyses by hormone type require large numbers of exposed cases, as well as detailed prospective information on prescribing. The GPRD has both, and sufficient information to allow adjustment or stratification by known potential confounders such as body mass index and alcohol use (as well as some less well-established risk factors for breast cancer such as smoking and use of aspirin).

Finally, a major source of evidence on the effects of exogenous sex hormones on breast cancer risk has been, and will continue to be, the results from pooled reanalyses of individual data included in the international Collaborative Group on Hormonal Factors in Breast Cancer mentioned above. The proposers of the current study also run this collaboration; collaborative results are currently being updated for both hormonal contraceptives and for hormone therapy for the menopause, and a comprehensive and up to date analysis of GPRD data would allow the optimal contribution from GPRD to the worldwide evidence.

Study type

Hypothesis testing and confirmation of findings of public health significance.

Study design

Nested case-control study within defined cohort in GPRD, using cases and controls matched for age, practice and observation time in the GPRD. 2 controls will be selected per case to maximise study power.

Study population

Women aged 20-79 years registered with GPRD on or after 1 January 1995.

Inclusion criteria:

- Age 20-79 [age group includes almost all cancers and hormone prescriptions]
- Registered with GPRD up –to-standard practice on or after 1 January 1995
- Fulfilling GPRD acceptable patient criteria
- At least 1 year in GPRD before index date (date of diagnosis of case)

Exclusion criteria:

- Previous invasive or *in situ* breast cancer

Case selection

Cases will be identified as any eligible patient with an incident diagnosis of invasive or *in situ* cancer of the breast between 1 January 1995 and latest available date.

Selection of comparison group (controls)

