2 controls per case selected from eligible patients who do not have a medical diagnosis of breast cancer documented at any time up to the latest available date (above). This includes diagnoses of breast cancer prior to or during the study period. Controls and cases matched on age (within 2 years), practice and observation time in GPRD (ie controls to have observation time in GPRD at least as long as their matched case, to allow exact matching in the analysis; for cases, start date of observation = most recent of patient registration date, practice up-to-standard date and practice management start date, end date (index date) = date of diagnosis). Index date for controls defined as the diagnosis date of their matched case.

Sample size and power calculations

Incidence of invasive breast cancer in GPRD is similar to that in the general UK population, which is ~63 per 100,000 per year (Office for National Statistics (ONS), 2007) ie 630 cases per million person years. There are currently 62 million person years of research acceptable followup in GPRD (GPRD Gold October 2010 release), so we might expect some 39,000 incident breast cancers in the whole database, and of these about 20,000 will be in women aged 50-75 (ONS, 2007). It seems reasonable to assume, allowing for some restriction of age group and observation time, that our analyses would include at least 10,000 breast cancer cases and 40,000 controls. These numbers are consistent with those in the GPRD study by Opatrny et al, which included incident cases of invasive breast cancer in women aged 50-75 diagnosed between 1998 and 2004, and had over 6,000 cases [14]. From the Opatrny study and from our previous analyses in GPRD (protocol no. 10_006; analyses not yet published) the prevalence of HT prescribing in women over 40 years will be approximately 33 % (possibly lower in very recent years); OC prescribing in women 20-50 years is estimated at about 20 % in GPRD in recent studies of outcomes other than cancer [16].

With these numbers the study will be amply powered with 80% power and 95% confidence to detect a minimum relative risk of <1.1 in relation to overall risk for HT or OC use v no use, and of <=1.5 for any subgroup with exposure prevalence of 1% or more.

Exposures, outcomes, covariates

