Validation studies have shown GPRD outcome and exposure (prescription) data to be sufficiently reliable and complete for epidemiological analysis; and the GPRD population is sufficiently representative of the UK population for the results to be broadly generalisable.

Potential limitations of the GPRD for these analyses include the lack of complete information on smoking, alcohol and body mass index, and particularly on reproductive factors such as parity, breastfeeding history and age at first birth; and the fact that information on prescribing of hormonal contraceptives is likely to be incomplete, as prescriptions issued outside general practice will not always be recorded. It is estimated that 80% of all prescriptions for hormonal contraceptives in the UK are issued in general practice (UK Family Planning Organisation, personal communication). Data on other potential confounders, such as diet and socioeconomic status, are not available (the impact of the latter will to some extent be minimised by matching of cases and controls by GP practice).

Such missing data will have the effect of diluting the study power, but should not introduce bias unless data is missing for reasons related to the outcome. The consistency of the results of previous HT studies in GPRD with those from studies in which reproductive factors were taken into account argues against substantial bias in the database; similar comparisons will help in interpreting results on hormonal contraceptive use. Sensitivity analyses with restriction to patients with full data on adjustment variables (complete case analysis) will be performed to test the effect of missing data in the main analyses.

Use of other prescribed drugs which may affect breast cancer risk (eg bisphosphonates, NSAIDs) cannot readily be taken into account by adjustment as there are complex possible relationships between prescribing of these drugs and of HT. Stratified analyses will allow these factors to be taken into account to some extent.

Plans for communicating and disseminating results

We aim to publish the results of this study in a peer-reviewed journal at the earliest opportunity. Study results will also be submitted for presentation at an appropriate scientific meeting. There are no restrictions on the extent or timing of publication.

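### The limitations section says missing data should not bias results unless missingness relates to outcome; this is untrue of unrecorded contraceptive use and of covariates coded as unknown

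*Protocol*

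**What the plan says.** In the protocol section on limitations of study design, data sources and analytic methods, three kinds of gap are listed: incomplete smoking, alcohol, body mass index and reproductive data; contraceptive prescriptions issued outside general practice; and confounders with no data at all. On the second it adds: "It is estimated that 80% of all prescriptions for hormonal contraceptives in the UK are issued in general practice". The next paragraph takes these together. They dilute power, it says, but "should not introduce bias unless data is missing for reasons related to the outcome". It then plans a complete-case sensitivity analysis on the adjustment variables, and cites the agreement of earlier hormone therapy (HT) studies in the database as evidence against substantial bias.

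Two other sections determine how the gaps enter the analysis. Under exposures, outcomes and covariates, a woman is exposed if she has at least one recorded prescription in the observation period. There is no category for uncertain exposure, so everyone else is unexposed. Under the statistical analysis outline, "Adjustment variables will include smoking status (never, current, past, unknown), alcohol drinking (none, some, unknown"), and body mass index and parity are given an unknown level in the same way.

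**The concern.** The sentence applies one rule to two different problems and is untrue of each.

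For exposure, the gap does not show up as a missing value. A woman supplied by a clinic outside general practice is moved into the reference group. That is misclassification, and it biases a non-null odds ratio even when it has nothing to do with outcome.

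For covariates, an unknown level controls confounding only among women whose value is recorded. Within the unknown stratum nothing is controlled, whether or not missingness is related to outcome.

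At stake is what the contraceptive odds ratios can support. The background puts the relative risk for current oral contraceptive use at about 1.3, and the sample-size section claims power to detect less than 1.1. Small systematic errors are not reduced by adding cases, which is what the 2017 amendment does.

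**Working it through.** **1. The plan's own precision, for scale.** Inputs from the sample-size section: "with 80% power and 95% confidence"; "our analyses would include at least 10,000 breast cancer cases and 40,000 controls"; HT prevalence 33%; "OC prescribing in women 20-50 years is estimated at about 20 % in GPRD". Exposure among cases is p1 = p0·OR / (1 − p0 + p0·OR). Solving a two-sided comparison of two proportions for OR (unmatched approximation) gives minimum detectable odds ratios of 1.068 (33% exposed), 1.080 (20%) and 1.335 (1%). The stated limits of below 1.1 and at most 1.5 therefore reproduce. The design section plans two controls per case, not four; at that ratio the figures are 1.075, 1.088 and 1.372, still within the limits.

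The amendment reports 33,000 cases and 66,000 controls already extracted. At 33% exposure, the standard error of the log odds ratio near the null is √[1.5 / (33,000 × 0.33 × 0.67)] = 0.0143, so the 95% limits are about ×/÷ 1.03. With 10,000 cases they are about ×/÷ 1.05. The contraceptive analysis is restricted to ages 20–50 and will be less precise.

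**2. Unrecorded contraceptive use.** Assumptions: recorded prevalence in controls is 20%; capture per woman s is the same in cases and controls; no false positives. True prevalence is 0.20/s. At s = 0.80 it is 25%, so missed users make up (0.25 − 0.20)/0.80 = 6.25% of the apparently unexposed controls. Writing u for that fraction,

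observed OR = OR / [1 + u(OR − 1)].

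- True 1.30: 1.30 / (1 + 0.0625 × 0.30) = 1.276.
- True 2.0: 2.0 / (1 + 0.0625 × 1.0) = 1.882.
- True 1.0: 1.0, no bias.

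The 80% in the protocol counts prescriptions, not women, so s is varied for a true 1.30:

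| Capture per woman | 95% | 90% | 80% | 70% | 60% | 50% |
|---|---|---|---|---|---|---|
| Observed OR | 1.295 | 1.289 | 1.276 | 1.260 | 1.238 | 1.209 |

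For a rare exposure (1% recorded) at 80% capture, 1.30 becomes 1.299, which is negligible.

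**3. Unknown levels.** The documents give neither missingness rates nor confounder strengths, so all inputs here are assumptions. An expected-count logistic model was fitted with one binary confounder (prevalence 35%), no true exposure effect, and the confounder missing completely at random.

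| Confounder OR with exposure / with outcome | Crude | Unknown level, 30% missing | Unknown level, 50% missing | Complete-case |
|---|---|---|---|---|
| 2.5 / 1.65 (strong) | 1.12 | 1.035 | 1.059 | 1.000 |
| 1.5 / 1.3 (weak) | 1.026 | 1.008 | 1.013 | 1.000 |

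The residual log odds ratio is close to the missing fraction times the crude one: 0.5 × ln 1.12 = 0.057, or 1.058. If the confounder–exposure association is reversed in the weak case, the residuals are 0.993 and 0.988, so the direction depends on the confounder.

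**4. Do the planned checks cover this?** The complete-case analysis recovers the true value for covariates here. It is restricted by completeness of adjustment variables, so it leaves exposure errors untouched. Requiring two or more prescriptions tightens the definition of exposed and cannot find a user with none recorded. No analysis of missed users is described.

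**The case against.** The strongest reply is that the plan is more careful than the one sentence suggests, and much of this stands.

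- A reader might infer that the plan claims missing data do nothing but cost power. It does not: it excepts outcome-related missingness and lists incomplete and unavailable confounders as limitations.
- A reader might infer that unknown categories are the only handling, or that the complete-case check is a poor one. The complete-case analysis is planned, and under the plan's own condition it removes the covariate bias. Its cost is precision. If half the women had full data, independently, 0.5 × (1 − 0.5²) = 37.5% of 1:2 sets would remain informative. Of 33,000 sets that is about 12,400, more than the 10,000 cases used for power, though the loss would weigh more on ages 20–50.
- A reader might infer that confounding is left wholly in place. The estimate lies between crude and fully adjusted; at 30% unknown about 70% of the log-scale confounding is removed.
- The exposure bias is small at the only figure the protocol gives. One recorded prescription suffices, so capture per woman may exceed 80%; it could also be lower.

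The appeal to earlier HT studies carries less weight. It says nothing direct about unrecorded contraceptives, and the background states that the authors know of no earlier study of contraceptives and cancer in this database.

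**Conclusion.** The sentence is wrong as written and should be corrected. For contraceptives, non-differential under-recording moves a non-null use-versus-no-use odds ratio towards 1: 1.30 to 1.28 and 2.0 to 1.88 at an assumed 80% capture per woman, and 1.30 to between 1.295 and 1.21 over 95% to 50%. For covariates, the unknown levels leave a residual odds ratio of about 1.01 to 1.06 under the illustrative inputs; the upper end needs strong confounding and half the values unknown.

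It would be tempting to conclude that all contraceptive odds ratios will be too small. The documents do not support that: there is no bias at a true odds ratio of 1, the direction is not assured when hormone types are compared with one another, and the effect nearly vanishes for rare exposures. Nor does this extend to HT, for which no recording shortfall is given. Nor do the documents show that multiple imputation must be the main model; it is one sound choice among others.

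**What to change.** - Rewrite the limitation in two parts. For exposure: unrecorded contraceptive use is expected to attenuate non-null use-versus-no-use odds ratios even when unrelated to outcome, with direction not assured between types. For covariates: an unknown level leaves part of the confounding even when values are missing at random.
- Add a simple bias analysis of the contraceptive odds ratios over a range of capture per woman that includes 80%, noting that the protocol's 80% counts prescriptions.
- Do not rest adjusted conclusions on the unknown-category model alone. Report beside it either the complete-case estimate or a multiple-imputation estimate whose imputation model includes case status, hormone exposure and the matching factors. State in advance which estimate governs if they differ.

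The cost is a few sentences and some analysis time, with no new data. Complete-case analysis loses precision; imputation relies on data being missing at random given the recorded variables, which should be stated.
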